If the optimised programme is effective, a secondary objective of the RISE project is to explore the implementation and scalability of PLH-YC to enable wide-spread and sustained use of the optimised parenting programme in the Southeastern European countries. We will apply the steps of the RE-AIM model [38] to translate the learning from implementation of the evidence-based programme into sustainable practice. Moreover, we will report on the cost-effectiveness of the programme and other service use by parents in the PLH-YC and control conditions during, and after the intervention across the three countries.

The secondary aims and hypotheses are:
Examine the cost-effectiveness of PLH-YC in comparison to a lecture on parenting on the *primary outcome* of child aggressive behaviour and the economic impact of the programme, including potential costs for future dissemination and scale-up. Impact on other outcomes such as dysfunctional parenting, positive parenting, and child quality of life will also be used to better inform decision-making.To assess the role of socio-economic, contextual and individual factors (i.e. family adversity, parental mental health, intimate partner violence, couple dissatisfaction, and child aggressive behaviour at baseline) on the implementation of PLH-YC in the three countries. We will examine implementation in hypotheses a–c in two ways. We will examine these associations with enrolment (attended 1st session) across groups. We will also examine the associations with participation rate in the PLH-YC condition (percentage of sessions attended). The hypotheses are:

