Higher family adversity at baseline assessment—including higher poverty, household hunger, parental mental health problems, intimate partner violence, and couple dissatisfaction will be associated with reduced participation in the PLH-YC group and lower enrolment across groups;Higher child aggressive behaviour at baseline will be associated with increased participation and enrolment by parents;Higher programme participation and enrolment will be associated with greater improvements in the primary and secondary outcomes;Higher programme fidelity and quality of delivery by facilitators of PLH-YC will be associated with greater improvements in the primary and secondary outcomes.We also hypothesise that indirect effects such that the above listed baseline variables (a and b) will predict enrolment, participation rate, and programme fidelity, which in turn will predict improvements in primary and secondary outcomes.*Additional Moderation Analyses*: Based on previous literature [27, 39, 40], we advance additional moderator hypotheses that pertain to parental, family, and child characteristics. Regarding parent/family characteristics, the hypotheses are as follows: (a) where parents have higher levels of baseline mental health problems, intervention effects on child aggressive behaviour will be greater in the PLH-YC compared to the control condition; (b) where parents have higher levels of baseline dysfunctional parenting, intervention effects on child aggressive behaviour will be greater for the PLH-YC condition compared to the control condition; (c) there will be no moderation effect of higher poverty, household hunger, and parental relationship dissatisfaction on the primary outcome child aggressive behaviour. The hypotheses related to child factors as moderators of intervention effect on the primary outcome are the following: (a) where children have higher levels of baseline child aggressive behaviour, intervention effects on aggressiveness will be greater, and (b) there will be no moderation effect of child gender or age on the primary outcome child aggressive behaviour (although gender may moderate outcome if associated with baseline level of child aggressive behaviour).

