### Participants and eligibility criteria

Potential parents or other primary caregivers will have the following inclusion criteria: (a) be aged 18 years or older, (b) be responsible for the care of a child between the ages of 2 and 9; (c) report at least subclinical levels of child’s behavioural problems as assessed with the oppositional defiant disorder subscale (ODD) of the Child and Adolescent Behavior Inventory (CABI, scores ≥ 10 will be included) [41, 42]; (d) have spent at least four nights a week with the child in the same household during the previous month and will continue to do; (e) agree to being randomised to one of the conditions; (f) consent to participate in the full study; (g) have adequate language skills to participate in the group /lecture, either in the primary language of the group or with additional language support provided. We will exclude primary caregivers whose children have been removed from their custody.

Inclusion criteria for facilitators are as follows: 1) aged 18 or older, 2) prior participation in a training workshop for the lecture/PLH-YC, 3) agreement to either deliver the lecture (one session) or PLH-YC (five sessions), 4) provision of consent to participate in the full study.

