#### Interventions

##### Control group

Parents allocated to the active control arm will receive a structured power-point presentation on parenting and child development issues, called “Raising Healthy Children” (duration: 1 to 1.5 hours). The structure and contents were developed by University of Bremen and reviewed by the project partners, and the material is available upon request. Four topics will be covered: (1) Stages of child development; (2) Potential risk factors for child internalising problems; (3) Resources and protective factors; (4) Tips: What parents can do to promote children’s development. The choice of this comparator was made so as to ensure that parents from the active control benefit from useful information in dealing with their children (given that all recruited participants reported having a child with elevated levels of behavioural difficulties will have children with behavioural problems). At the same time, when conceiving the lecture, we made sure we minimised the effects of potential confounds in the control group that would make it similar to the intervention, such as details on parenting strategies, programme length, non-didactic approach (lecture in this group versus collaborative work in the intervention group), and hands-on activities (no home activities for this group).

Facilitators delivering this lecture will have the same/similar expertise to that of the facilitators engaged in PLH. Facilitators will participate in a brief training explaining the purpose of the lecture, clarifying the contents and addressing potential concerns. They will also be trained to follow the protocol to minimise risk of contamination between the two conditions (e.g. only allow minimal discussion within the lecture, answer questions in a didactic way).

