##### Intervention group

The optimised version of PLH-YC will be delivered over five weekly sessions using a participatory, non-didactic approach to engage parents in learning positive parenting and child behaviour management skills. Programme activities include illustrated comics modelling how to implement key parenting skills, home activity assignments to apply these skills with their children, and group discussions addressing challenges experienced when applying home activities. The programme also includes simple mindfulness stress reduction exercises such as “Taking a Pause” to help parents cope with stress and reactivity towards their children. There is a facilitator manual for each session, and parents receive a PLH parent book (long versions in English, Macedonian, and Romanian available here: https://rise-plh.eu/work-packages/work-package-2/). For the current study, the facilitator manuals and parent handbooks of the optimised intervention will also be translated into Albanian and Russian. If the programme is delivered in person according to the standard protocol, each PLH-YC group with 12 parents will be delivered by two facilitators. Locally recruited professionals and non-professionals (e.g. teachers, psychologists, social workers, and peer parents) with prior experience delivering the programme during Phase 2 of the RISE project will serve as facilitators. All facilitators participated in a 40-h standardised training prior to delivering the programme for the first time. They will also receive an additional 16-h booster training prior to the RCT.

Programme and lecture delivery will start as soon as the programme implementers can organise a group of approximately 12 participants per condition who have completed baseline assessments. Facilitators of both groups will receive supervision on demand by trained coaches who have also previously provided coaching to facilitators during Phase 2.

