#### Implementation outcomes

*RE-AIM Reach measurements* will comprise enrolment rate (total number of caregivers who attend the first session of the PLH/ the lecture group divided by the number of families recruited in that condition) and, for the PLH groups, the participation rate (percentage of the five sessions attended).

With regard to *RE-AIM implementation quality*, for both groups, programme implementation will be assessed in terms of implementation fidelity and adherence. The number of total activities actually implemented (yes/no), divided by the number of activities by facilitator (assessed via a facilitator checklist) required in the PLH-YC programme manual/lecture content, will be used as an indicator of *implementation fidelity.* Fidelity assessments will be self-reported by facilitators as well as assessed by external raters during live coded sessions (see below).

For *quality of delivery*, *competent adherence* of PLH facilitators to the programme activities and their delivery skills will be assessed with the PLH-Facilitator Assessment Tool (PLH-FAT) [32]. Trained assessors will attend one to two sessions to do live codings using the PLH-FAT. Seven distinct behavioural categories will be grouped into two scales, describing core activities and process skills. The assessment of core activities comprises modelling skills, collaborative work between facilitators, engaging participants, and leadership skills. Coaches assessing facilitators will not be blind to allocation. The delivery skills of the lecture facilitators will be assessed with one overall quality of delivery item (0 = inadequate, 4 = excellent), which will be rated by trained coders.

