##### Primary and secondary outcome analyses

Data will be analysed using an intention-to-treat approach, in line with the study protocol and with good practice in RCTs [70]. Missing data will be handled using either multiple imputation or Full Information Maximum Likelihood (FIML) method [71].

The primary analysis will consist of testing comparatively the magnitude of change in child aggresive behaviour, in the control vs. PLH-YC participants, at post-test and follow-up. Identical analyses will be run for the secondary outcomes (i.e. child internalising problems, dysfunctional parenting strategies, positive parenting, daily reports of effective parenting behaviour, child maltreatment, parental mental health, IPV, couple satisfaction, parenting stress, quality of parent-child relationship, and child ’s quality of life). The main analyses will involve testing pre-post or pre-follow-up differences controlling for pre-intervention levels whilst accounting for covariates. Maximum likelihood estimation with robust statistics will be used with Mplus 8.2 software to account for non-normal distributions in measures and also apply a FIML framework for handling missing data at post- or follow-up. The models will be further tested using latent growth curve models adjusting for country and pre-assessment levels of the outcome variables (e.g. age as a time-invariant covariate). Indirect effect models will be tested in a structural equation framework and include participation rate and fidelity as mediators for the PLH-YC group and enrolment rate as the mediator across groups. In additional analyses, we will also model the effects of participation (i.e., attendance). This will be analysed with Complier Average Cause Effect models that estimate the magnitude of the paths based on the baseline scores in predictors (e.g. family adversity) and actual participation [72]. Further clustering will be within groups (facilitators) and included in subsequent analyses as needed. The analyses for MINI-KID ODD/CD positive screen will be conducted with logistical regression models due to the categorical nature of the data. Depending on the distributions and on other descriptive indicators, Bayesian analyses will be used as deemed appropriate.

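### One enrolment-to-outcome path across both arms mixes attending a complete one-session lecture with merely starting a five-session programme

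*Protocol article*

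**What the plan says.** **Definition.** The section on aims describes two ways of examining implementation in hypotheses (a) to (c). One is participation rate within PLH-YC. The other is enrolment: "We will examine these associations with enrolment (attended 1st session) across groups". The section on implementation outcomes counts enrolment as the "total number of caregivers who attend the first session of the PLH/ the lecture group", divided by the number of families recruited in that condition.

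**Use.** Hypothesis (c) under the secondary aims reads: "Higher programme participation and enrolment will be associated with greater improvements in the primary and secondary outcomes". The same section adds indirect effects running from baseline characteristics through enrolment, participation and fidelity to outcome. The section on primary and secondary outcome analyses says the structural equation models will "include participation rate and fidelity as mediators for the PLH-YC group and enrolment rate as the mediator across groups".

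**Treatments.** "The optimised version of PLH-YC will be delivered over five weekly sessions". The lecture is a single session (abstract; eligibility criteria for facilitators). The control-group section says of its design that "we made sure we minimised the effects of potential confounds in the control group that would make it similar to the intervention", and lists detail on parenting strategies, length, teaching style and home activities as the features kept apart.

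**The concern.** The same value of the enrolment indicator has a different meaning in each arm. For a lecture parent it marks complete receipt of a treatment kept light on parenting strategies. For a PLH-YC parent it marks the start of a longer treatment with different content. If one coefficient links this indicator to outcome, two problems follow:

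- **Mixing.** The coefficient averages two effects that there is no reason to think equal, with weights set by attendance in each arm.
- **Self-selection.** Parents who turn up may do better whatever they are offered. The lecture arm gives some information on this, and a common slope averages that information away.

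At stake is the interpretation of hypothesis (c) as it concerns enrolment, and of the indirect paths through enrolment. A positive common slope could come from a working programme, from motivated attenders, or from both.

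**Working it through.** The protocol gives no effect size, uptake or power for the enrolment path, so there is no stated figure to reproduce.

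**Step 1: what enrolment represents.** Share of sessions implied by attending the first = 1 / number of sessions.
- Lecture: 1/1 = 100%.
- PLH-YC: 1/5 = 20% as a minimum, because an enrolled parent may attend up to all five.

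**Step 2: what a common slope estimates.** Let b_P and b_L be the enrolment-to-outcome slopes (improvement, in SD) in PLH-YC and the lecture, and p_P and p_L the uptake. Arms are equal in size (1:1 randomisation). With arm in a linear model,

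common slope = [b_P·p_P(1−p_P) + b_L·p_L(1−p_L)] / [p_P(1−p_P) + p_L(1−p_L)].

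Assumed, not in the protocol: p_P = 0.75 and p_L = 0.90. The weights are 0.75 × 0.25 = 0.1875 and 0.90 × 0.10 = 0.09, which sum to 0.2775.
- Programme works, lecture does nothing (b_P = 0.33, b_L = 0), arm in the model: 0.33 × 0.1875/0.2775 = 0.22.
- Same truth, arm left out: 0.33 × 0.75/(0.75 + 0.90) = 0.15.
- Neither treatment works but attenders improve 0.20 more in both arms: 0.20.

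An effective programme (0.22) and pure self-selection (0.20) give almost the same common slope. By arm they separate: 0.33 and 0 in the first case, 0.20 and 0.20 in the second.

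**Step 3: sensitivity to uptake.** Hold the slopes at assumed values of b_P = 0.30 and b_L = 0.05 and vary only attendance, with arm in the model.

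| Uptake PLH-YC / lecture | Weights | Common slope |
|---|---|---|
| 80% / 80% | 0.16, 0.16 | (0.048 + 0.008)/0.32 = 0.175 |
| 85% / 65% | 0.1275, 0.2275 | (0.03825 + 0.011375)/0.355 = 0.14 |
| 70% / 90% | 0.21, 0.09 | (0.063 + 0.0045)/0.30 = 0.225 |

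Simulation gave 0.17, 0.14 and 0.23 for these rows. Over all the pairs simulated (b_P 0.25 to 0.30, b_L 0 to 0.10), the arm-adjusted common slope ran from about 0.10 to 0.23. It moves with attendance while the effects stay fixed, and an arm-by-enrolment term recovers the two slopes.

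**Step 4: what separating the arms costs.** Take 864/2 = 432 per arm, residual SD 1 (assumed) and uptake as in step 2. The information is 432 × 0.1875 = 81 in PLH-YC and 432 × 0.09 = 38.9 in the lecture.
- SE of the pooled slope: 1/√(81 + 38.9) = 0.091.
- SE of the slope difference: √(1/81 + 1/38.9) = 0.195.
- Power for a true difference of 0.33 at two-sided 0.05: 0.33/0.195 = 1.69, and Φ(1.69 − 1.96) ≈ 39%, before dropout.

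**The case against.** The strongest reply is that the protocol never states an equality constraint. Naming enrolment as the mediator across groups may only say where the variable exists: enrolment is defined in both arms, participation rate only in PLH-YC. Path constraints in a secondary structural equation model can properly be left to the analysis plan, which is not shown. This stands in part. A reader might infer that arm will be left out of the model, and the text does not say so. Still, the sentence presents enrolment as one mediator for both arms, against two confined to PLH-YC, and the only multi-group analysis named is by country. A common path is the natural reading.

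Four further points stand and limit the concern:

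- **Dose.** A reader might infer that enrolled PLH-YC parents receive one-fifth of the treatment. One-fifth is only the floor.
- **Other analyses.** Dose is covered by participation rate within PLH-YC, and non-random attendance by the planned complier average causal effect models. Neither mixes the arms' exposures.
- **Wording of hypothesis (c).** It is associational. If attenders in both arms improve more, it is true as written. The trouble comes only if that result is read as an effect of PLH-YC uptake.
- **Scale-up.** A reader might infer that the path drives the reach or scale-up conclusions. The protocol does not route it there: reach uses the enrolment rate itself, and large-scale resource needs are based on the cost-effectiveness results.

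It is also tempting to make the slope difference the formal test of hypothesis (c). The working does not support that. Power is low, and with unequal uptake the non-attenders are different subsets of parents in each arm, so the lecture slope is not a clean control for self-selection.

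**Conclusion.** The point holds for one secondary implementation and mediation analysis. First-session attendance marks full receipt in the lecture arm and at least a start in PLH-YC. A single path from it to outcome is an uptake-weighted mixture, which cannot by itself show that taking up PLH-YC improves outcomes. In the illustration a true 0.33 SD appears as 0.22 or 0.15, and self-selection alone appears as 0.20.

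These sizes rest on assumed uptake and effects. The mixing itself needs only that the slopes differ between arms. The conclusion also rests on reading the mediator sentence as a common path, which is the natural reading but not an explicit statement. The intention-to-treat comparison, the within-PLH-YC participation analysis and the complier models are unaffected. This is a cheap improvement to a secondary analysis, not a threat to the trial's main result.

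**What to change.** In the section on primary and secondary outcome analyses, or in the analysis plan, state that:

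- models using enrolment include arm, and the enrolment-to-outcome path is estimated by arm, through an arm-by-enrolment term or a multi-group model;
- both slopes and their difference are reported with confidence intervals, the difference being exploratory and not the sole test of hypothesis (c);
- the lecture slope is read as an informative but imperfect indicator of self-selection;
- any pooled slope is presented only as a descriptive association;
- pooled enrolment is kept as the dependent variable for hypotheses (a) and (b), with arm in the model. A common definition is reasonable there, because the question is who turns up.

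This changes wording only and uses data already planned. The cost is wider intervals: under the step 4 assumptions, the standard error of the difference is roughly twice that of the pooled slope.

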#### Group allocation and allocation concealment

Prior to randomisation, all countries will identify and select a sample of recruitment sites (schools, kindergartens, community, and social services centres) covering different neighbourhoods, geographical areas, ethnic compositions, and socio-economic strata in and around Skopje (North Macedonia), Cluj-Napoca (Romania), and Chișinău (Republic of Moldova).

Randomisation will be coordinated by one of the project partners (University of Klagenfurt) using an online randomiser, https://www.randomizer.org/ (*N* = 288 per country, 864 in total). Participant numbers will be randomised to the PLH-YC programme or the control condition after completion of the baseline assessment based on the randomisation list (individual 1:1 randomisation in blocks of 24). The randomisation list will be provided to the team in Bremen, who will be contacted after each participant is enrolled to unveil their assignment. This threefold procedure allows the analysis team to remain blind to group assignment, ensures that assignment occurs independently and ensures that teams in each country receive allocation information after enrolment.

Participants will be allocated to groups after completion of the pre-assessment. Thus, outcome assessors and participants will be blinded to group allocation at pre-assessment. All data assessors conducting pre-test, periodic, post-test, and follow-up interviews with parents will be blinded regarding the allocation of participants to the groups to minimise evaluation bias: The implementation of the intervention will be conducted by different staff (programme coordinators and facilitators) than the assessments. Thus, data assessors will be unaware of the group allocation of participants at the later assessment points (periodic, post, follow-up). To ensure that participants do not reveal their group allocation during the post- and follow-up assessment to the assessor, the data assessor will ask the participants to not share the group allocation at the beginning of the interview. Only in cases where the parent reports a (serious) adverse event, will the group allocation be unblinded (during periodic  and follow-up assessments). Upon completion of the pre-test measurements, caregivers will be notified of their allocation status.

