#### Data analysis

##### Sample size calculation

To allow detection of small effect sizes, we will estimate sample size based on a *d* = .25 (*f* = .10) for the primary outcomes. Detecting this effect in a repeated measures ANOVA at an alpha of .05 whilst ensuring a power of 80% requires a total sample of *N* = 704. We will examine the change in the primary outcomes across three time points (pre, post, and follow-up) within the overall sample using latent growth modelling and conduct a multi-group analysis to test differences across countries. To reach the required sample size of 704, we will recruit a total of 864 families for baseline assessment, assuming approximately 17% drop-out rate based on our previous phase of data collection [69].

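### Families are treated in groups, but the main model has no delivery-group term and clustering is left to later discretion; if the primary test omits it, type I error exceeds .05 whenever the within-group correlation is positive

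*Protocol article*

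**What the plan says.** The section on group allocation specifies "individual 1:1 randomisation in blocks of 24", so the family is the unit of randomisation. Treatment is then delivered in groups. Under standard delivery "each PLH-YC group with 12 parents will be delivered by two facilitators", over five weekly participatory sessions. The lecture is a single session of 1 to 1.5 hours, also for about 12 participants. The COVID contingency plan reduces PLH-YC groups to six parents with one facilitator; online lectures stay at 12.

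The sample size section arrives at 704 analysable families in the sentence that begins "Detecting this effect in a repeated measures ANOVA at an alpha of .05 whilst ensuring a power of 80% requires a total sample of". Its only inflation is for loss to follow-up: "To reach the required sample size of 704, we will recruit a total of 864 families for baseline assessment". The allowance is about 17%, taken from the project's preceding phase. It mentions no ICC, group size or design effect.

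The section on primary and secondary outcome analyses describes the main analysis as a baseline-adjusted comparison with covariates, followed by growth models that adjust for country. Robust maximum likelihood is justified by non-normal distributions. After the mediation and complier analyses comes the one sentence on clustering: "Further clustering will be within groups (facilitators) and included in subsequent analyses as needed". No criterion for need is given.

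The aims also include a hypothesis about delivery itself: "Higher programme fidelity and quality of delivery by facilitators of PLH-YC will be associated with greater improvements".

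**The concern.** This is an individually randomised, group-treated design. PLH-YC parents share facilitators, sessions and discussion for five weeks, so their outcomes may be correlated. The article's own hypothesis that facilitator fidelity and quality drive improvement implies such a correlation in the PLH-YC arm. A model that treats the families in a group as independent then gives too small a standard error for the arm contrast, intervals that are too narrow, and a test that rejects too often. Robust standard errors aimed at non-normality do not correct this.

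The article does not simply leave the matter to an analysis plan. It raises clustering, then places it in later analyses and makes it optional. That leaves the validity of the primary test to an undefined judgement.

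The fidelity hypothesis has a related problem. Fidelity and delivery quality vary between groups or facilitators, not between families within a group. The 432 PLH-YC families (864/2) form only 432/12 = 36 groups, or 432/6 = 72 groups of six.

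**Working it through.** **1. The plan's own figure.** The stated inputs are "we will estimate sample size based on a *d* = .25 (*f* = .10) for the primary outcomes", alpha .05 and power 80%. For two groups f = d/2, so d = .25 is f = .125 and f = .10 is d = .20; the two values do not match. A simple two-group comparison needs 504 (d = .25) or 786 (d = .20). A two-group repeated measures ANOVA with f = .10 and an assumed correlation of .5 between time points needs 591 (two times) or 526 (three times) for the between-group effect, and 199 or 163 for the interaction. About 704 appears only with unstated inputs, for example f = .10 with a correlation of about .8 over two times (709). So 704 is not reproduced from what is stated. None of the near matches needed a clustering term.

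Drop-out: 704/0.83 = 849. Recruiting 864 allows for 1 − 704/864 = 18.5% loss, so it covers the stated 17%.

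**2. Inputs for the clustering check.**
- Analysed families per group: 12 × 704/864 = 9.8, and 6 × 704/864 = 4.9.
- Equal arms, from the 1:1 allocation.
- ICC: not given. Assumed .01, .02, .05 and .10, with 0 as the reference.

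**3. Formulas.** Design effect in a clustered arm: DE = 1 + (m − 1) × ICC. For the arm contrast, average the DE of the two arms; an unclustered arm has DE = 1. Actual two-sided type I error of a test that ignores clustering: 2 × [1 − Φ(1.96/√DE)].

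Example, groups of 12, ICC .05. In the clustered arm DE = 1 + 8.8 × .05 = 1.44. With both arms clustered, 1.96/√1.44 = 1.633, giving 10.2%. With PLH-YC only, DE = (1.44 + 1)/2 = 1.22 and 1.96/√1.22 = 1.775, giving 7.6%.

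**4. Results: type I error if clustering is ignored.**

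| ICC | 12s, PLH-YC only | 12s, both arms | PLH-YC in 6s, PLH-YC only | PLH-YC in 6s and lecture in 12s, both arms |
|---|---|---|---|---|
| 0 | 5.0% | 5.0% | 5.0% | 5.0% |
| .01 | 5.5% | 6.0% | 5.2% | 5.7% |
| .02 | 6.0% | 7.1% | 5.4% | 6.5% |
| .05 | 7.6% | 10.2% | 6.1% | 8.8% |
| .10 | 10.2% | 15.3% | 7.3% | 12.5% |

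**5. Simulation check.** A baseline-adjusted model with heteroscedasticity-robust standard errors was simulated with 352 families per arm in 36 groups of about 10, both arms clustered, 4,000 runs. It rejected a true null in 5.0%, 5.6%, 10.4% and 16.4% of runs at ICC 0, .01, .05 and .10. This agrees with the formula and confirms that robust errors without a group term do not restore the level.

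**6. Power.** If 704 gave exactly 80% without clustering, a cluster-adjusted test with both arms clustered in twelves would have Φ(2.80/√DE − 1.96) = 73%, 65% and 53% at ICC .02, .05 and .10. If instead the comparison is a simple one at d = .25, 704 gives 91% without clustering and 86%, 79% and 68% with the same design effects. The gap between the two sets shows how far the answer depends on the unreproduced starting point.

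**The case against.** The strongest reply is that inflation requires two things the article does not establish: a positive ICC, and a primary model that actually omits clustering. At ICC 0 there is no inflation, and at .01 it is about one percentage point or less. The clustering sentence is loose enough that a clustered primary model could still be run. A reader might infer that the primary test definitely exceeds 5%, or that the choice will be made after the data are seen. The text supports neither: it gives no ICC, and it does not say when or how need is judged. The claim must therefore be conditional.

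A second reply concerns the scenario. Equal clustering in both arms is a weak leading assumption, because the lecture is one didactic session with only minimal discussion. Only PLH-YC falls to six. This also stands, which is why the PLH-YC-only and six/twelve cases are shown. They reduce the inflation but do not remove it.

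Third, a reader might infer that the trial is too small or falls below 80% power by a known amount. The article does not support that, because 704 cannot be reproduced and a simple comparison at d = .25 would start from 91%.

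Finally, the clustering sentence directly follows the mediation and complier analyses and may be meant for them, including fidelity. Even so, optional clustering does not secure the right unit for a fidelity effect, and that reading leaves the primary model with no clustering provision.

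**Conclusion.** The point holds in conditional form. Followed as written, the main model has no delivery-group term, and nothing in the article commits the primary test to one. If it is omitted, the type I error exceeds .05 for any ICC above zero. Under standard groups of 12 the excess runs from about half a percentage point (ICC .01, PLH-YC only) to about ten points (ICC .10, both arms). With PLH-YC in sixes and ICC .05 the error is about 6.1% (PLH-YC only) or 8.8% (both arms, lectures in twelves). These figures rest on assumed ICCs, loss spread evenly over groups, and equal arms.

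The stated 80% power takes no account of clustering, so it is not the power of a cluster-adjusted test. The amount lost cannot be fixed from the article.

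**What to change.** Replace the clustering sentence with a commitment along these lines: the primary and all other outcome models account for assigned delivery group from the outset, whatever the observed ICC, for example by a random group effect allowed to differ by arm or by cluster-robust standard errors. Analyse fidelity and delivery quality as group-level predictors in a two-level model.

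Keep 864 families; the trial status section reports recruitment complete. Restate power with a design effect over a range of ICCs that includes 0 and .01, after reconciling d = .25 with f = .10 and stating the inputs behind 704.

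The cost is mostly wording, with three real downsides. Intervals widen by √DE: about 10% at a design effect of 1.22 (√1.22 = 1.10), up to 37% at 1.88 (√1.88 = 1.37). The stated power becomes less favourable. Each family must be linked to its assigned group; the article does not say that this link is recorded, although using fidelity as a mediator in the PLH-YC arm would already require linking families to groups or facilitators.
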